**G. Data Handling and Record Keeping**

## G1. Confidentiality and Security

Electronic data will be housed on the secure server of the WFSM. The electronic database will contain the participant’s unique project identifier, medical record number, and full date elements, but will otherwise be clean of PHI. A key will be maintained linking the participant’s project ID number to their PHI, and will be stored by the WFSM, Department of Emergency Medicine in a locked office. Access to PHI will be restricted to the project team members, IRB, adjudication committee, and auditors. Data entry will be performed by trained research staff with valid confidentiality agreements.

## G2. Data Handling

Data will be processed using methods currently used by this project team. A detailed “sources of data” document describing the source of each data point will be created. Data collection templates will be integrated into REDCap. Validation rules will be applied to data as they are entered to reduce data queries. Automated reports will be generated displaying data quality assessments and form completion rates for discussion in Operations Meetings.

## G3. Training and Quality Assurance

A detailed manual of procedures (MOP) will be developed and contain definitions of all measurements and descriptions of all project procedures. This manual will be developed by the PI with assistance from the project staff. The MOP will be housed on a central server for project team access.

The research unit has implemented standard operating procedures for conducting clinical trials, specific to interacting with ED patients. The members of this research unit are trained on these procedures. The research unit has regularly occurring meetings to discuss vulnerable populations, recruitment progress, data quality, and workload.

The PI will train the primary coordinator on the project protocol and project procedures. The primary coordinator will then train other project team members. All project team members will be trained according to the Project Training List in the Manual of Procedures prior to project initiation.

## G4. Case Report Forms and Source Documents

Electronic case report forms will be used. Data whose original source is the electronic medical record will not be printed as it will be housed on the electronic medical record system of the hospital.

## G5. Standardization of Measurements

The manual of procedures will contain detailed descriptions of all project measurements. Standard definitions for measurement classifications have been chosen when available, and an adjudication committee will be used to determine more subjective measurements.

## G6. Performance Monitoring

Oversight of the project will be conducted by the PI. Data will be reviewed for completeness periodically by the PI. If data inconsistencies are noted, corrective actions will be taken.

**H. Data Quality Monitoring**

## H1. Data Quality Monitoring Plan

The PI will periodically review project data for quality and completeness. If data inconsistencies are noted, corrective actions will be taken and more frequent monitoring will occur.

Data tables will be examined by the PI / project staff periodically to determine missing data and to examine for implausible values. Electronic data queries will be generated for the project coordinator.

**I. Recruitment and Timeline**

Prior to beginning this pilot 3 months will be needed for training and project start-up. Following this start-up period, we anticipate a 12 month pilot project period will be required to obtain the 500 participants needed for this pilot. The pilot period will be followed by a 3 month close-out period to complete follow-up phone calls and record reviews.

| Project Timeline | | |
| --- | --- | --- |
| Summer 2016 | 2016-17 | 2017 |
| 3 months | 12 months | 3 months |
| Start-Up | Pilot Project | Close-Out |

**J. Protection of Human Subjects**

J1. Risks to Human Subjects

Overview: The HEART score with i-STAT POC troponin testing has been selected for local EMS system implementation based on collaborations across multiple disciplines including Emergency Medicine, Cardiology, and Prehospital Care. As a clinical quality improvement implementation with broad-based support, participation by human subjects will be part of customary care within the ambulance and upon arrival at WFBMC ED. Following implementation patients treated for acute chest pain by Forsyth, Stokes, and Surry County EMS and at WFBMC ED will have index and outcome data abstracted from an investigational pre-hospital record and the WFBMC EMR. In addition, as is customary in EMS quality surveillance patients will be contacted by phone to assess for adverse events. These data will be reviewed to ensure the feasibility and accuracy of a prehospital chest pain risk assessment using the HEART score with POC i-STAT troponin measurement. Quality surveillance activities will be performed under a waiver of informed consent, obtained from the Institutional Review Board, as is currently utilized for similar quality surveillance programs at WFBH (i.e. the HEART Pathway Implementation). Validation of thei-STAT troponin device in a moving ambulance will be completed concurrently by comparing POC and core-laboratory troponin results.

a. Human Subjects Involvement and Characteristics

The HEART Score pilot implementation has support from county and state EMS medical directors with a planned roll out in 2016. Planning is currently underway including coordination with the WFBH Point-Of-Care-Testing Committee and Abbott Laboratories Inc. Quality surveillance is being conducted to ensure the feasibility of this implementation (the accuracy and reproducibility of the HEART score as determined by paramedics in the field). Patients will receive standard care (which following implementation in 2016 will include HEART score calculation and POC troponin testing). Data will be collected from paramedic records, the WFBH EMR, and telephone follow-up calls. However, we are interested in publishing the findings of this implementation project. Therefore this project meets the definition of human subjects’ research.

For the pilot implementation we anticipate a sample size of approximately 500 subjects accrued over a 12 month period. Based on prior studies we expect about 90% to have complete follow-up data. We intend to exclude subjects who were less than 21 years old at the time of their ED visit, were having an acute ST-segment elevation MI (STEMI), or were inter-facility transfers. We anticipate this population will consist of an equal proportion of male and female patients of mean age 56 years based upon our preliminary data. Subjects will likely have increased cardiovascular risk factors compared to a normal population of controls. Subjects may have a history of cardiovascular disease. No special populations of subjects will be included. No collaborating sites will identify subjects. Specific inclusion and exclusion criteria are:

### Inclusion Criteria

1. Age greater than or equal to 21
2. Non-traumatic chest discomfort or other symptoms consistent with possible ACS
3. Patient being transported to WFBMC ED for further care

### Exclusion Criteria

1. ST-segment elevation in contiguous leads on any electrocardiogram (>/= 1 mV)
2. Inter-facility transfers
3. Short Pre-hospital times: Scene time + Transportation time anticipated to be less than 5 minutes.
4. Unstable vital signs: symptomatic hypotension at the time of enrollment (systolic < 90 mm Hg), tachycardia (HR>120), bradycardia (HR<40), and hypoxemia (<90% pulse-oximetry on room air or normal home oxygen flow rate)
5. Known terminal diagnosis with life expectancy less than 1 year
6. Concomitant non-cardiac medical, surgical, or psychiatric emergency

b. Sources of Materials

**Description of research material**

Research material obtained from the human subjects will include clinical data. Recorded data will include: demographic information, historical and physical exam data, laboratory results, radiologic and cardiac imaging results, diagnoses, clinical outcome information, all collected retrospectively.

**Description of data to be collected**

Data from the prehospital encounter, index hospital visit, and 30 day follow up period, including demographics, historical and physical exam data, laboratory results, radiologic and cardiac imaging results, diagnoses, length of stay, clinical outcome information and invasive procedures will be abstracted by the project team from EHR. Adverse events (MACE) will be identified by record review and by phone follow-up calls at 30-90 days after the index encounter.

**Access to individually identifiable private information**

Access to individually identifiable private information will be limited to those people required to access this information in order to conduct this project. This includes project team members, IRB, adjudication committee, and data monitors.

The project database will contain a limited amount of individually identifiable private information in the form of whole date elements and medical record numbers. Each participant will be assigned a unique sequential project identifier that will be linked to the participant’s research record and source documents through a log housed locally. Access to the entire project database will be limited to project team members at WFBMC who are involved in the trial management activities, including project team members, the institutional review board (IRB), adjudication committee, and data monitors.

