Paramedics will use a worksheet to obtain the historical and clinical data needed to calculate a HEART score. This will include performing POC troponin testing. This is within the scope of practice of paramedics who routinely perform venipuncture and POC testing on acutely ill patients. Furthermore, the feasibility of performing POC troponin analyses in a moving ambulance has been previously established. Given the paramedic’s need to use the POC troponin value for HEART score calculation they cannot be blinded to the troponin results. However, during this pilot, they will not deviate from their normal chest pain triage and destination plans based on the results. The routine chest pain triage and destination plans for these EMS counties include obtaining an IV, ECG, and the administration of aspirin, nitroglycerin, and supplemental oxygen. Also, during this pilot, i-STAT troponin and HEART Score results will not be used to determine or alter the patient’s transportation destination.

Since paramedics are not blinded to POC troponin results we will not prevent them from sharing their i-STAT troponin results with the ED care team as part of their typical transfer of care reports. However, they will do so using a study specific form, which clearly states that this POC troponin value is for study purposes only and is not to be used to determine a patient’s clinical care. We will train ED nurses and providers that EMS POC troponin results are part of a pilot, should not be acted on clinically at this time, and require confirmation with a core-lab troponin. While the ED care team will receive report on the POC troponin results (as well as the patient’s clinical features and ECG, as part of a normal EMS verbal report), the ED care team will remain blinded to paramedics’ HEART Scores to allow evaluation of agreement between paramedic and ED provider risk assessments. HEART Score calculation by the ED provider is part of the standard ED care for patients with acute chest pain presenting to the WFBMC ED, which will facilitate assessment for agreement. Paramedic POC troponin results and HEART Scores will not become part of the patient’s medical record.

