## E. Project Procedures

## E1. Clinical Data Collection

For quality assurance data collection, participants will be identified retrospectively and data will be collected electronically using EHR (EMS records, and WFBH medical records) and via telephone follow-up calls.

Paramedics will use a worksheet to obtain the historical and clinical data needed to calculate a HEART score and this will include recording the POC troponin results. This worksheet will be an investigational record integrated into their normal reporting workflow. Data entered on this worksheet will be abstracted retrospectively. Data obtained will include demographic information (age, gender, race, ethnicity), date and time elements, characteristics of chest pain, ECG interpretation, cardiac risk factors (such as, prior coronary artery disease, smoking, hypertension, diabetes, hyperlipidemia, etc), POC troponin value, and the HEART score.

Since all participants will be transported to WFBMC ED, where the HEART Pathway is part of standard care, we will use the electronic medical record (EMR) to obtain ED physician HEART Score assessments and WFBMC troponin results. These data will be compared to paramedic assessments for determination of inter-observer agreement and correlation. We will also use the EMR to track index outcomes and 30 day events that occur within the WFBH system. Data collected from the WFBH EMR will include patient demographics, history and physical examination data, past medical history, cardiovascular risk factors, ECG results, laboratory results, HEART score and HEART Pathway assessments, ED and discharge diagnoses, disposition, index visit length of stay, objective cardiac testing at the index visit or within 30 days, recurrent ED visits, re-admissions, coronary revascularization, and MI or death within the follow-up period.

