## E4. Endpoint Adjudication

A consensus of two reviewers ([name], [name]) will adjudicate elements required to measure the occurrence of all MACE endpoints. Reviewers will adjudicate return visits to the ED or readmissions within the ED are cardiac related if this unclear based on preliminary review by project staff. To make these assessments, reviewers will be provided the participant’s index and discharge records, records obtained from follow-up including claims data when available, and project definitions. Records will have patient identifiers removed. Reviewers will complete a reviewer outcome form recording the occurrence of safety endpoints, which will be stored in our secured electronic database. Any disagreements will be settled by consensus between the two reviewers, or the involvement of a third reviewer ([name]).

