**Collection, management, and protection of research specimens, records, and data Collection**

Data from the prehospital encounter, index visit, and 30 day follow up period, including patient demographics, history and physical examination data, past medical history, cardiovascular risk factors, ECG results, laboratory results, HEART score assessments, ED and discharge diagnoses, disposition, index visit length of stay, objective cardiac testing at the index visit or within 30 days, recurrent ED visits, re-admissions, coronary revascularization, and MI or death will be abstracted from the EHR and supplemented by phone follow-up calls. These data will be entered into a locally maintained and secured electronic database using the REDCap system. Validation rules will be applied to data as they are entered to reduce data queries. Automated reports will be generated displaying data quality assessments and form completion rates for discussion in Operations Meetings.

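### The access rule lets the MACE adjudicators open the entire project database, which holds the paramedic HEART score and ambulance troponin under test, and nothing in the protocol masks them to it

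*Protocol*

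**What the plan says.** **Access.** Section J1, under Access to individually identifiable private information, sets the limit: "Access to the entire project database will be limited to project team members at WFBMC who are involved in the trial management activities", and continues "including project team members, the institutional review board (IRB), adjudication committee, and data monitors". The committee that decides the outcome is thus on the list for the whole database.

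**Content.** Section E1 has the paramedic worksheet abstracted for the project. Its fields include "POC troponin value, and the HEART score". The overview of J1 says index and outcome data are "abstracted from an investigational pre-hospital record and the WFBMC EMR". The data-collection paragraph of J1 covers the prehospital encounter, lists "laboratory results, HEART score assessments, ED and discharge diagnoses" among the items, and says they are entered in REDCap.

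**Adjudication.** Section E4 has two reviewers decide all MACE endpoints by consensus, with a third available. They receive index and discharge records, follow-up records and the definitions. The only masking step is "Records will have patient identifiers removed".

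**Related safeguards.** The Methods part of the abstract says "Paramedic POC troponin results and HEART Scores will not become part of the patient’s medical record". The abstract, D1 and D4 blind the ED side to the paramedic's HEART score. No section gives the adjudicators an equivalent protection.

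**The concern.** MACE is the reference standard against which the paramedic score is judged. Section E2 counts a MACE in a patient scored low-risk as a missed MACE, so a reviewer who knows the paramedic's score also knows whether a borderline ruling will count against the primary hypothesis.

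There is some room for judgement. The MI definition in E2 combines a troponin change with evidence such as ischaemic symptoms. One cardiac-death category is an unexpected death presumed to be ischaemic. Section G5 says the committee exists for the more subjective measurements.

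The protocol already accepts the principle, since it blinds ED providers to the paramedic score to protect the agreement aim. The accuracy aim, which carries the sample size, has no matching rule. As written, a report could not cite the protocol to show that outcomes were adjudicated blind to the index test, and this cannot be repaired once adjudication is done.

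**Working it through.** **Step 1. Can reviewers reach the index test?**

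| Question | Where | Answer |
|---|---|---|
| Who decides MACE? | E4 | Two reviewers, third if needed |
| May they use the whole database? | J1, access paragraph | Yes, the committee is named |
| Are paramedic score and ambulance troponin abstracted? | E1 | Yes |
| Do prehospital data and HEART scores enter the database? | J1, data collection | Yes |
| Does any section mask reviewers to them? | E4 and elsewhere | No, identifiers only |

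The route is open on paper.

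**Step 2. Is the packet itself free of risk information?** Paramedic results stay out of the medical record, so a packet built from the hospital chart would probably lack them. Two items could still disclose them or something close to them. The ambulance troponin is passed to the ED team on a study-specific form. The ED physician's HEART score sits in the electronic record (E1) and is expected to agree with the paramedic's. E4 excludes neither.

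**Step 3. How much can one ruling move the primary result?** Inputs from F2 and F3: target sensitivity 98%, lower 95% bound above 90%, 50 events, 10% MACE rate, exact binomial intervals.

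- The plan's own figure: N = events / rate = 50 / 0.10 = 500. Reproduced.
- Misses allowed at target: 50 × (1 − 0.98) = 1.
- Sensitivity = x / n, where n is adjudicated MACE and x is those scored high-risk.
- Exact (Clopper-Pearson) lower bound = the 0.025 quantile of Beta(x, n − x + 1). When x = n this is 0.025^(1/n).

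| Scenario | x / n | Sensitivity | Exact lower bound |
|---|---|---|---|
| One miss, counted | 49/50 | 98.0% | 89.4% |
| That miss ruled not MACE | 49/49 | 100% | 0.025^(1/49) = 92.7% |
| Two misses, total held at 50 | 48/50 | 96.0% | 86.3% |
| One further low-risk case ruled MACE, added to 49/50 | 49/51 | 96.1% | 86.5% |

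A ruling on a low-risk case changes the numbers as follows. Ruling the single miss out removes it from the denominator and raises sensitivity by 2.0 points. Ruling one more in adds it to the denominator and lowers sensitivity by 98.0 − 96.1 = 1.9 points, almost the same as two misses in a fixed 50. The first change also takes the exact lower bound from below to above the 90% named in F2.

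**The case against.** The strongest reply is that the J1 sentence is a confidentiality limit. It caps who may have access and does not tell reviewers to consult every field. E4 is the operative text, and its list of materials includes neither the database nor the worksheet. The committee may be named only because its outcome forms are stored there. J1 and J2 describe access control by user, area and role, and G3 leaves detailed procedures to a manual that is not shown. Discretion is also bounded: revascularization is a procedural fact, MI needs a troponin value above the 99th percentile with a rise or fall plus a further criterion, and two reviewers must agree.

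Most of this stands, and it limits the claim to what is permitted. It does not remove the claim. The role controls are described as a capability and are nowhere applied to adjudicators, and the written rule names the committee for full access.

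Three stronger readings may tempt a reader, and the documents support none of them:

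- **That adjudication will be unmasked in practice.** Permission to open a field does not show that anyone will.
- **That the primary result will be biased by a stated amount.** The table in the working shows how fragile a 50-event sensitivity is to any reclassification, masked or not. No figure in the documents says how many borderline low-risk cases to expect.
- **That the identifier lists are a second breach of masking.** G1 says "Access to PHI will be restricted to the project team members, IRB, adjudication committee, and auditors", with similar lists in J1, J2 and J5, while E4 works from de-identified records. That wording should be reconciled, but it concerns who the patient is, not what the paramedic scored. Editing it would not mask the index test.

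**Conclusion.** The point holds as a gap in the written safeguards. The protocol permits adjudicators to see the index test and masks them only to identity. The size of any resulting bias cannot be estimated from the documents. What can be shown is the leverage: with 50 events, one ruling on a low-risk patient moves sensitivity by about 2 points and can carry the exact lower bound across 90%.

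This rests on two assumptions: that the worksheet fields are entered in the project database, as E1 and J1 together indicate, and that about 50 MACE events occur, as F2 plans. The project is an observational pilot that does not alter triage, so no patient's care depends on this. Its accuracy estimate is nevertheless meant to support a larger implementation, so the change should be made before adjudication begins.

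**What to change.** 1. **J1, access paragraph.** Remove the adjudication committee from the list with access to the entire database. Give reviewers a role limited to the de-identified packet and the reviewer outcome form.
2. **E4.** State that reviewers are masked to the paramedic HEART score, the ambulance point-of-care troponin (including the study-specific hand-over form) and the ED HEART score until all outcome forms are locked. The access change alone would leave the ED score in the packet.
3. **G1, J1 (Data Management), J2 and J5.** Reconcile the identifier-access lists with E4's de-identified records. This is a secondary wording point.

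The cost is a few sentences, one user-role setting in a system that J2 says can assign access by role, and removal of the scores and the hand-over form when the packet is prepared. It adds no patients, visits or data, and the sample size is unchanged. The one drawback is that a reviewer who is also on the project team needs restricted access until outcomes are locked.
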